### Interim analyses {21b}

Interim analyses will be performed, and we will stop the trial based on interim data analysis, namely if clearly one treatment is better than the other.

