### Sample size {14}

Using GPower 3.1 (University of Kiel, Kiel, Germany), this experiment is a factorial design, and the parameters required for this experiment are not found in previous studies. Based on the expected results of the experiment, a small effect size of 0.2 [15], two-sided A = 0.05, test power (1-β) of 0.9, and the F-test are taken to calculate the sample size of 220 cases. To compensate for an estimated 20% loss to follow-up, the final total sample size is 264 cases.

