## Assignment of interventions: blinding

### Who will be blinded {17a}

We do not blind the evaluators of the result scale and physical examination but only group them after baseline data collection to avoid the impact of subjective bias on baseline data. In the subsequent result evaluation, the evaluators of the scale and physical examination are not blinded, only the laboratory testers of HbA_1c_ are blinded, and the data analysis personnel are not blinded either.

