## Statistical methods

### Statistical methods for primary and secondary outcomes {20a}

Data will be analyzed applying SPSS 23.0 (IBM, Chicago, IL, USA). Data will be expressed as mean ± standard deviation or as *n* (%) in the case of categorical data, and differences between the four groups will be assessed for significance using the chi-squared test in the case, analysis of variance in the case, or non-parametric rank-sum test in the case of skewed continuous data. Differences between different time points within each group will be assessed for significance using generalized estimation equation. These models will include intervention variables, time as a categorical variable represented by dummy variables, the interaction between intervention and time, and baseline values. Differences associated with *P* < 0.05 will be considered significant.

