### Composition of data monitoring committee, its role and reporting structure {21a}

This is a low-risk intervention and Ethics Committee of the First Affiliated Hospital of Chengdu Medical College does not require one.

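### The protocol fixes an efficacy stop in subjective words, with no named comparison among four arms, and keeps the final test at 0.05, so overall type I error exceeds 5% by an amount the document leaves undetermined

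*Protocol article*

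**What the plan says.** Four parts of the Protocol article bear on this point.

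- **Interim analyses {21b}.** The commitment is definite and plural: "Interim analyses will be performed". The stopping criterion is that "we will stop the trial based on interim data analysis, namely if clearly one treatment is better than the other". The section has no further rule.
- **Sample size {14} and Statistical methods {20a}.** The design uses "two-sided A = 0.05", and the analysis section says "Differences associated with *P* < 0.05 will be considered significant". Neither makes an allowance for earlier looks.
- **Who will be blinded {17a}.** Evaluators of scales and physical examination are unblinded, and "the data analysis personnel are not blinded either". Only the laboratory testers of HbA1c are blinded.
- **Data monitoring committee {21a}.** There is none, on the ground that the intervention is low-risk and the ethics committee does not ask for one. The steering committee in {5d} is made up of project leaders, researchers and funders.

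The trial has four arms (Control, Reminder, App, App + Reminder) in a factorial layout. The possible comparisons therefore include two main effects, an interaction and several pairwise contrasts.

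**The concern.** A rule that allows a trial to stop and claim superiority at an interim look uses up part of the type I error. If the final test then still uses the full 0.05, the total exceeds 0.05. Here the interim criterion is also a matter of judgement, because 'clearly' has no number and 'one treatment' against 'the other' does not pick out a contrast when there are four arms. Whoever looks at the data could choose both the comparison and the bar after seeing the results.

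Two things are at stake. The first is the 5% error rate behind the trial's main claim, which cannot be defended for a rule of this kind. The second is the size of the reported effect, because trials that stop on a favourable interim overestimate it on average. Neither blinded analysis nor an independent committee is in place to limit either problem. The rule can also operate in practice: the trial began in October 2021, follow-up lasts 6 months, and recruitment was expected to run to the end of 2023, so month-6 HbA1c data accrue while recruitment continues.

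**Working it through.** **Inputs from the document.** Two-sided alpha 0.05 ({14}); final threshold P < 0.05 ({20a}); more than one interim analysis, with number, timing, contrast and threshold not given ({21b}).

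**Assumptions, because the document gives no figures.** A single contrast; K equally spaced looks including the final one; a stop counts as a claim of superiority; interim threshold P < 0.05, P < 0.01 or P < 0.001; final critical value 1.96.

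**Formula.** Overall error = 1 − P(|Z₁| ≤ c₁, …, |Z_K| ≤ c_K) under the null, where corr(Z_i, Z_j) = √(t_i/t_j) for i < j and t_i = i/K.

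**The plan's own figure.** With no interim look, 2 × P(Z > 1.96) = 0.050. The stated alpha is reproduced only in this case.

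**One interim at half the information** (correlation √0.5 = 0.707):

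- Interim at 0.05 (c₁ = 1.96): 0.0500 + 0.0331 = 0.0831.
- Interim at 0.01 (c₁ = 2.576): 0.0100 + 0.0446 = 0.0546.
- Interim at 0.001 (c₁ = 3.291): 0.0010 + 0.0492 = 0.0502.

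**One to four interims:**

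| Interims | Judged at P < 0.05 | Judged at P < 0.01 | Judged at P < 0.001 |
|---|---|---|---|
| 1 | 8.31% | 5.46% | 5.02% |
| 2 | 10.73% | 5.85% | 5.05% |
| 3 | 12.62% | 6.19% | 5.08% |
| 4 | 14.17% | 6.50% | 5.11% |

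Timing matters less than the threshold. A single interim at P < 0.05 gives 9.1% at 25% of the information and 7.3% at 75%. For the four-group test (3 degrees of freedom) with one interim at P < 0.05, simulation gives about 8.5%.

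**Overestimation after an early stop.** Take a true effect for which the full trial has 90% power on one contrast. The expected final z is 1.96 + 1.28 = 3.24, and the expected z at half the information is 3.24 × 0.707 = 2.29. With an interim at P < 0.05:

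- Chance of stopping in the right direction: P(Z > 1.96 − 2.29) = 0.63.
- Mean z among trials that stop: 2.29 + φ(−0.33)/0.63 = 2.29 + 0.378/0.63 = 2.89.
- Ratio to the truth: 2.89/2.29 = 1.26, so the estimate at stopping is on average about 26% too large.

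**Check on a repaired design.** One look at half the information at P < 0.001, followed by a final test at 0.0498 (0.04978 unrounded), gives an overall two-sided error of 0.050.

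**The case against.** The strongest reply is that this is a journal article. The number, timing and boundary of interim looks commonly sit in a full protocol or analysis plan, and neither is shown here. That is right as far as missing detail goes, and the point does not rest on it. It rests on what the article does fix: a subjective superiority stop alongside a flat 0.05.

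The second reply concerns size. Section {20a} does not apply P < 0.05 to the interims, and 'clearly' may well suggest a stricter bar. This stands. A reader might infer that the trial's error rate is 8% or 14%, but the document does not support any single figure, and at P < 0.001 the excess is negligible.

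A reader might also take 'one treatment better' to mean any of the six pairwise comparisons, each at P < 0.05, and reach about 20% with no interim and about 31% with one. Section {20a} plans an overall comparison of the four groups, not six unadjusted pairwise tests. The 20% is also multiplicity that arises without any interim look.

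Third, the primary outcome is measured by blinded testers at one certified external laboratory. That protects the HbA1c assay, so unblinded analysts do not imply biased HbA1c measurement. It does not protect the decision to stop. Nor does the article say who takes that decision. That the trial team would take it is a plausible inference, not a stated fact.

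**Conclusion.** The concern holds in a limited form. As written, {21b} cannot be followed while keeping the 5% error rate in {14} and {20a}, because any efficacy look with a positive chance of stopping under the null adds to a final test at the full 0.05. The direction is certain, provided that a stop counts as a claim of superiority.

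The size is not determinable from the document. It depends on the number of looks, their timing, the contrast and the meaning of 'clearly', and it runs from practically nothing to nearly three times the nominal rate (14.2/5 = 2.8) across the assumptions tabulated. That spread is itself the defect, because the rule leaves the error rate to judgement exercised on unblinded data. Overestimation after an early stop follows under any of these thresholds. The 26% figure applies only to one half-way look at P < 0.05 with a true effect at 90% power.

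**What to change.** **Preferred.** Delete the efficacy stop from {21b} and state that no interim efficacy analysis will be done. Because the trial has been running since October 2021, say 'no further' if a look has already occurred. In that case report when it was, what was compared, who saw it and what was decided. Nothing else in the article depends on an efficacy stop: the intervention is described as low-risk and follow-up is 6 months.

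**If a look is kept.** Specify one look, when half the month-6 HbA1c data are in (about 110 of the plan's 220), on one named comparison, the App main effect. Stop only at P < 0.001, and do the final test at 0.0498 (0.05 would give 5.02%). The App main effect must then be named in {20a}, which at present describes four-group comparisons. Say who sees the interim result and who decides. An estimate from an early stop should still be reported as likely to be too large, since a strict boundary protects the error rate but does not remove that bias.

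**Cost.** An amendment to {21b}, and to {20a} if a look is kept, with the ethics committee approval that {25} requires. The loss is a small chance of stopping early. At the P < 0.001 boundary and a true effect with 90% power, that chance is P(Z > 3.29 − 2.29) = 0.16. No change to the sample size is needed.

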### Methods for additional analyses (e.g., subgroup analyses) {20b}

We may analyze by comparing two study sites or educational levels.

### Methods in analysis to handle protocol non-adherence and any statistical methods to handle missing data {20c}

Data will be analyzed based on intentionality analysis. The extent to which data may be missing will be analyzed and examined, especially in view of the main findings of the study. Missing values are filled with the last data. For example, for participants without the 3rd month follow-up, the baseline data will be filled in. For participants with 3rd month follow-up but without 6th month follow-up, the 3rd month data will be filled in.

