**Methods:**

This will be a 2-center, factorial design, equal proportional distribution, superiority trial conducted in outpatient endocrinology clinics at two tertiary hospitals in Chengdu, China. The trial will enroll smartphone-literature individuals at least 18 years old who have been diagnosed with T2DM based on glycosylated hemoglobin (HbA_1c_) of at least 7.0%. Individuals will be randomly assigned to receive routine care with standard education about T2DM and glycemic control (Control), routine care as well as weekly telephone reminders to self-monitor blood glucose (Reminder), routine care and a smartphone application providing information about glycemic control and health management with T2DM (App), or the combination of routine care, the smartphone application, and weekly telephone reminders (App + Reminder). After 6 months of these interventions, participants will be analyzed for the primary outcome of HbA_1c_ as well as the secondary outcomes of blood glucose monitoring frequency, body mass index, blood pressure, knowledge about diabetes, health beliefs related to diabetes, diabetes self-management behavior, and satisfaction with the smartphone application.

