### Outcomes {12}

Data are collected at three times, including two follow-up visits at baseline, the 3rd month after intervention, and the 6th month after intervention, through participant visits to the hospital by the investigator.

The primary outcome is the level of HbA_1c_, which reflects blood glucose levels over the preceding 2–3 months and is a good indicator of blood glucose control [10, 11]. All results will be made by high-performance liquid chromatography at the same certified external laboratory to ensure consistency.

Secondary outcomes include frequency of blood glucose monitoring, body mass index, blood pressure, knowledge about diabetes, health beliefs related to diabetes, and diabetes self-management behavior. The App and the App + Reminder groups will also be asked about their satisfaction with the smartphone application.

The following questionnaires will be used for the study:

Change in knowledge from baseline as measured by the Chinese version of the Diabetes Knowledge Questionnaire (DKN) [12]. Each item is scored from 0 to 1, and the total scores range from 0 to 23 (Higher score indicating greater knowledge of diabetes)Change in health belief from baseline as measured by the Health Belief Questionnaire (HBQ) [13]. Scores ranging between 20 to 100 (higher score indicating better outcomes)Change in self-management behavior from baseline as measured by the Type 2 Diabetes Self-management Behavior Scale (2-DSCS) [14]. Total scores range from 26 to 130 (higher score indicating better outcomes)Custom-made questionnaire to assess user satisfaction with Dnurse application and its paired glucose meter. Participants who use the APP 6 months after the intervention will complete the assessment. The 5-level Likert scoring method is adopted, and the total scores range from 11 to 55 points (Table 2)

**Table 2 Tab2:** Custom-made questionnaire to assess user satisfaction with Dnurse application

Item	Very satisfied	Satisfied	Neither satisfied nor dissatisfied	Slightly dissatisfied	Very dissatisfied
1. Your satisfaction with the application interface					
2. Your satisfaction with the application’s ease of use					
3. Your satisfaction with how the application records blood glucose					
4. Your satisfaction with the health information provided by the application					
5. Your satisfaction with using the application to manage diabetes					
6. Your satisfaction with the application’s safety					

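### Carrying the last HbA1c value forward is the only stated missing-data method; it can shrink the App effect, or bias it either way if loss differs by arm and HbA1c falls in all arms

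*Protocol article*

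**What the plan says.** The missing-data section (20c) of the protocol article sets the analysis population, "Data will be analyzed based on intentionality analysis", and then one general rule: "Missing values are filled with the last data". Two cases are spelled out. With no month-3 visit, "for participants without the 3rd month follow-up, the baseline data will be filled in". The second case reads: "For participants with 3rd month follow-up but without 6th month follow-up, the 3rd month data will be filled in". The only other commitment is descriptive: "The extent to which data may be missing will be analyzed and examined, especially in view of the main findings of the study". No other method is named.

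The rule is not limited to particular outcomes, so it covers HbA1c, which is primary according to section 12 ("The primary outcome is the level of HbA_1c") and is measured at baseline, month 3 and month 6 (Table 1, section 18a). The sample size section (14) plans for substantial loss: "To compensate for an estimated 20% loss to follow-up", the target is 264. The statistical methods section (20a) names SPSS and a GEE with intervention, time, their interaction and baseline values.

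**The concern.** A filled value enters the model as if it had been measured. At 20% loss, about one month-6 HbA1c value in five would be a copy of an earlier one.

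A copied value misstates the 6-month result whenever HbA1c has changed since it was taken. Several features make a fall in every arm likely. Entry requires "glycosylated hemoglobin (HbA_1c_) of at least 7.0" percent, so some regression to the mean is expected. Section 11d lets drug treatment change during follow-up. All arms receive a meter (section 11a) and free test strips (section 11c). The documents give no figure for that fall.

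Unequal loss is also possible. The trial is open label, and the arms differ in app use, weekly calls and contact from the manufacturer. What is at stake is the size of the primary App effect, and under unequal loss also its direction of bias and the false-positive rate.

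**Working it through.** **Inputs from the protocol article.** N = 264, equal allocation, so 132 with App and 132 without; 20% loss overall, not split by arm; effect size 0.2; two-sided alpha 0.05. The plan gives no figure for the effect of missing data, so there is none to reproduce. Its 264 is 220 × 1.2, and nothing below depends on how 220 was obtained. Expected missing at month 6: 0.20 × 264 = 52.8, about 53.

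**Assumptions (not in the documents).** The effect size is Cohen's f, so the two-level App contrast is d = 2 × 0.2 = 0.4. The HbA1c SD is 1.5 points, so the true effect is 0.4 × 1.5 = 0.60. The correlation between visits is 0.5. Half of the 6-month change is reached by month 3 (g = 0.5). Drop-out is random within arm, and drop-outs would have changed as completers do.

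**Formula.** Let c be the fall without App, D the extra fall with App, d the loss in an arm, and h the share of drop-outs with a month-3 value. The share of the change that survives carry-forward is k = 1 − d(1 − hg). The expected estimate is k_App × (c + D) − k_noApp × c.

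**Equal loss of 20%, D = 0.60.** Here the c terms cancel.
- All carry baseline (h = 0): k = 0.80; 0.80 × 0.60 = 0.48.
- Half carry month 3 (h = 0.5): k = 1 − 0.20 × 0.75 = 0.85; 0.85 × 0.60 = 0.51.
- All carry month 3 (h = 1): k = 1 − 0.20 × 0.5 = 0.90; 0.90 × 0.60 = 0.54.

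The shrinkage is therefore 10–20%. In simulation with baseline-adjusted ANCOVA (132 v 132), power is 0.86 for carry-forward against 0.91 for observed data only if all carry baseline, and 0.89 against 0.93 if half carry month 3. Observed-data power does not depend on what is carried, so its spread of 0.91–0.93 is simulation noise. With no true effect, type I error stays near 5%.

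**Unequal loss, no true effect (D = 0).** The formula reduces to (k_App − k_noApp) × c. A negative value means that App looks worse than it is.

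| Loss App / no-App | Common fall c | Drop-outs carrying month 3 | Bias | Type I error |
|---|---|---|---|---|
| 25% / 15% | 0.8 | none | (0.75 − 0.85) × 0.8 = −0.08 | about 8% |
| 25% / 15% | 0.8 | half | (0.8125 − 0.8875) × 0.8 = −0.06 | about 6.5% |
| 30% / 10% | 0.8 | none | (0.70 − 0.90) × 0.8 = −0.16 | about 19% |
| 30% / 10% | 0.8 | half | (0.775 − 0.925) × 0.8 = −0.12 | about 12% |
| 30% / 10% | 0.8 | all | (0.85 − 0.95) × 0.8 = −0.08 | about 8% |
| 30% / 10% | 0.3 | none | (0.70 − 0.90) × 0.3 = −0.06 | about 7% |
| 30% / 10% | 0 | any | 0 | 5% |

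Reversing the arms reverses the sign. In the mildest combinations the rate is close to 5%: for example, fall 0.3 at 30%/10% with everyone carrying month 3 gives a bias of only (0.85 − 0.95) × 0.3 = −0.03.

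**Unequal loss, D = 0.60, c = 0.8, all carrying baseline.**
- App 25%, no-App 15%: 0.75 × 1.4 − 0.85 × 0.8 = 0.37.
- App 30%, no-App 10%: 0.70 × 1.4 − 0.90 × 0.8 = 0.26.
- App 10%, no-App 30%: 0.90 × 1.4 − 0.70 × 0.8 = 0.70.

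Observed-data ANCOVA recovers 0.60 and keeps type I error near 5% in every scenario.

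**Other outcomes.** Table 1 and section 18a schedule monitoring frequency at months 3 and 6 and satisfaction at month 6 only. Month-3 frequency can be carried to month 6. A missing month-3 frequency has no baseline to draw on, and a missing satisfaction score has no earlier value at all.

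**The case against.** The strongest reply is that the rule is transparent and, with equal loss, errs towards no effect, which is conservative in a superiority trial. False positives need two conditions together, unequal loss and a shared HbA1c change, and the documents give no figure for either. Test strips (section 11c) and visit subsidies (section 18b) are offered without distinction by arm, and section 20c undertakes to look at missingness against the main findings. All of this stands, and it limits the size of the claim.

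It does not rescue the rule. Under the plan's own 20% loss, a true effect is still understated if drop-outs change as completers do. Describing the extent of missing data does not correct the estimate. Nor is this a detail left to an unseen analysis plan, because the article itself fixes the method.

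A reader might also infer a larger power loss. An F-test without baseline adjustment gives 0.74 for carry-forward (f = 0.16, N = 264) against 0.82 for completers (f = 0.2, N = 211). The plan's GEE includes baseline values, so the baseline-adjusted loss of about 3–6 points is the relevant one.

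**Conclusion.** The concern holds in a conditional form. With equal loss, and drop-outs changing as completers do, carry-forward shrinks a true App effect by about 10–20% and costs a few points of power, without inflating type I error. With unequal loss and a common fall in HbA1c, bias follows the pattern of loss: more App loss hides benefit, more no-App loss inflates it. Null type I error is then about 6.5–8% at 25%/15% (fall 0.8) and about 7–19% at 30%/10%, apart from the mildest combinations. These figures rest on the assumed SD, correlation, common fall, month-3 fraction and loss by arm.

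Three stronger readings are tempting but unsupported:
- **Carry-forward always shrinks the effect.** It does not: 0.60 becomes 0.70 when the no-App arms lose more. If drop-outs truly return to baseline, carrying baseline causes no shrinkage.
- **Unequal loss alone creates a false effect.** With no common change, the bias is zero.
- **The rule cannot be applied to monitoring frequency at all.** It can carry month 3 to month 6; it fails only where month 3 is itself missing.

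**What to change.** In section 20c, replace carry-forward for the primary analysis by one of two methods:
- a likelihood-based mixed model on observed month-3 and month-6 HbA1c, with intervention, time, their interaction and baseline HbA1c as covariate (SPSS MIXED); or
- multiple imputation by randomised arm before the GEE already planned.

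Keep last-value carry-forward, if at all, as a labelled sensitivity analysis. State that satisfaction and a missing month-3 monitoring frequency cannot be filled by carrying a value forward, and say how they will be handled.

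The cost is a change of wording and a little more programming; no new data are needed. The drawback is reliance on a missing-at-random assumption, which a delta-adjusted sensitivity analysis can probe.

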### Plans to give access to the full protocol, participant-level data, and statistical code {31c}

The datasets analyzed during the current study and statistical code are available from the corresponding author on reasonable request, as is the full protocol.

